### Safety reporting

Both treatments’ safety will be evaluated through vital signs, physical exams, laboratory data, adverse events (AEs), and serious adverse events (SAEs). AEs encompass unexpected medical events or worsening conditions not necessarily linked to treatment, including hypophosphatemia, dizziness, diarrhea, nausea, vomiting, rash, fatigue, flatulence, and transaminase elevation. SAEs are events leading to death, life-threatening situations, hospitalization, deformities, birth defects, or significant permanent damages. AEs and SAEs will be documented in CRFs, with SAEs reported to ethics and administrative departments within 24 h.

Definition of the end of study is as follows: (1) participants have completed the last follow-up, (2) participants exhibit recurrence via imaging tests, and (3) participants die from any cause.

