### Exclusion criteria

The exclusion are as follows: (1) recurrent HCC; (2) concurrent HCV, HIV, or other serious infections; (3) other malignancies or mental illness; (4) prior anti-tumor therapies pre-surgery, including portal vein ligation/embolization, radiofrequency ablation, transarterial chemoembolization, etc.; (5) participation in conflicting ongoing trials.

Participants can withdraw at any time, and poor compliance may lead to removal. Withdrawal reasons will be recorded in case report forms (CRFs), and data will be analyzed following the intention-to-treat principle [22].

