### Endpoints

The primary endpoint is 3-year RFS, defined as the interval from the operation to the date of the first diagnosed HCC recurrence, recorded in months. The secondary endpoint is 3-year OS, defined as the interval from surgery to death or the date of the last follow-up, recorded in months.

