### Data collection and management

Investigators and coordinators will receive specialized training for data collection. All trial-related data will be recorded on study-specific CRFs. In particular, plenty factors, including different stages of cirrhosis, would play an important role in survival of patients with HCC after surgery. Comprehensive clinical data, including Ishak score of the resected specimen, fibrosis-4 index, aminotransferase-to-platelet ratio index, and other parameters for liver cirrhosis to evaluate the baseline stage of cirrhosis, will be prospectively collected. Besides, the death from decompensation of cirrhosis, HCC recurrence, and other reasons will be precisely recorded and recognized during the follow-up since decompensation in patients with cirrhosis is a competing event from HCC recurrence. Baseline assessments will be conducted pre-randomization, and missing data will be stored until received or confirmed as unavailable. Personal information will remain confidential. Data will be entered into Excel by two independent collectors, using participant numbers for identification. Access to information will be restricted. A data manager will oversee routine accuracy checks and address any issues with the investigators. Hard copy documents will be stored securely, and electronic files will have password protection. All documents will be saved for at least 5 years post-publication, with original data available upon request to the principal investigator.

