### Statistical analysis

Background measures will be presented as mean ± standard deviation for continuous variables or as numbers/percentages for categorical variables. Continuous variables will be compared using a two-sided student *t*-test or Mann-Whitney *U* test, while categorical variables will undergo the chi-square test or Fisher’s exact test. Patient survival (RFS and OS) will be calculated via the Kaplan-Meier method with log-rank test. In particular, cancer-specific survival will also be calculated since decompensation serves as a competing event from HCC recurrence for death. Stage of cirrhosis, tumor burden, antiviral regimen, and other factors which may affect survival after surgery would be considered when conducting survival analysis. Generalized linear models will analyze primary and secondary endpoints. An ITT analysis, including protocol deviations, will be conducted using IBM SPSS version 26.0 software. A *p*-value < 0.05 indicates statistical significance.

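### The end-of-study rule stops at imaging recurrence, which contradicts the 3-year OS endpoint, the recording of deaths from HCC recurrence and the planned cancer-specific survival

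*Protocol article*

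**What the plan says.** The end of study is defined at the close of the Safety reporting section: "Definition of the end of study is as follows: (1) participants have completed the last follow-up, (2) participants exhibit recurrence via imaging tests". The third item is death from any cause. All three items describe a state of the individual participant, and recurrence is listed beside death.

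Other sections ask for data that arise after recurrence:

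- **Endpoints:** "The secondary endpoint is 3-year OS, defined as the interval from surgery to death or the date of the last follow-up, recorded in months".
- **Data collection and management:** "the death from decompensation of cirrhosis, HCC recurrence, and other reasons will be precisely recorded and recognized during the follow-up".
- **Statistical analysis:** "cancer-specific survival will also be calculated since decompensation serves as a competing event from HCC recurrence for death".
- **Aims of the study:** the first aim is to compare recurrence risk and survival between the strategies.

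The Follow-up section and Table 1 schedule visits to 36 months. They do not say whether visits continue after a recurrence.

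On adherence, the Exclusion criteria section says "Participants can withdraw at any time, and poor compliance may lead to removal". The next sentence promises an intention-to-treat analysis.

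**The concern.** A death caused by HCC recurrence can only come after the recurrence. If recurrence ends the participant's study, that death falls outside the data. Under the OS definition the patient is then censored at the last follow-up, which is about the recurrence date.

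Kaplan-Meier and log-rank methods assume that a censored patient has the same outlook as those still at risk. A patient censored because the cancer has returned does not. If TDF lowers recurrence, as the trial supposes, more ETV than TDF patients are censored this way. A survival benefit or harm acting through recurrence would then be largely hidden from the OS comparison, and cancer-specific survival would lose most of its events.

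A smaller question concerns removal for poor compliance. The text does not say whether this is removal from study drug or from the study. If it is the latter, the promised ITT analysis lacks the later outcomes of those patients.

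**Working it through.** **Inputs from the protocol article.** Total 238, allocated 1:1, so 119 per arm. Planned 3-year RFS is 70% (ETV) and 85% (TDF). One-sided alpha 0.05, power 80%, 190 patients before a 20% dropout allowance.

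**Step 1: the plan's own figure.** A two-proportion comparison of 0.70 with 0.85 (pooled variance, no continuity correction, one-sided 0.05, 80% power) gives 95 per arm, or 190. Then 190 / 0.80 = 237.5, rounded up to 238. Both stated figures reproduce. They were set on RFS, so the end-of-study rule does not change them.

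**Step 2: patients the rule would remove from OS follow-up.** RFS is "defined as the interval from the operation to the date of the first diagnosed HCC recurrence, recorded in months", so one minus RFS is the expected proportion with recurrence (ignoring the few who die first).

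- ETV: 119 × 0.30 = 35.7
- TDF: 119 × 0.15 = 17.9
- Total: 53.6, about 54 of 238 (22.5%), with twice as many in the control arm

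**Step 3: follow-up time lost.** Assume a constant recurrence hazard, λ = −ln(RFS)/36 per month. Mean time under observation to month 36 is (1 − RFS)/λ.

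| Arm | λ per month | Mean months observed | Lost out of 36 |
|---|---|---|---|
| ETV | 0.00991 | 0.30 / 0.00991 = 30.3 | 5.7 (16%) |
| TDF | 0.00451 | 0.15 / 0.00451 = 33.2 | 2.8 (8%) |

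**Step 4: illustration of deaths missed.** The article gives no death rates, so those below are assumptions. The model has constant hazards: λ for recurrence, h0 for death without recurrence and h1 for death after recurrence. An annual probability a is converted by h = −ln(1 − a)/12. With s = λ + h0:

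- Death before recurrence by month 36: (h0/s)(1 − e^(−36s))
- Death after recurrence by month 36: (λ/s)(1 − e^(−36s)) − λ(e^(−36·h1) − e^(−36s))/(s − h1)

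Multiplying by 119 per arm and adding the arms:

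| Death per year without recurrence | Death per year after recurrence | Deaths before recurrence | Deaths after recurrence | Share missed |
|---|---|---|---|---|
| 1% | 5% | 6.2 | 4.1 | 39% |
| 1% | 10% | 6.2 | 7.9 | 56% |
| 1% | 15% | 6.2 | 11.5 | 65% |
| 1% | 40% | 6.2 | 26.8 | 81% |
| 2% | 5% | 12.4 | 4.0 | 25% |
| 2% | 10% | 12.4 | 7.8 | 39% |
| 2% | 15% | 12.4 | 11.4 | 48% |
| 2% | 40% | 12.4 | 26.6 | 68% |

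The missed share is 48–81% if death after recurrence is 15–40% per year, and 25–56% if it is 5–10% per year.

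**Step 5: effect on the comparison, for one row.** At 1% and 40% per year, total deaths are about 21.0 (ETV) and 12.1 (TDF). True 3-year OS is then 1 − 21.0/119 = 82% and 1 − 12.1/119 = 90%. The deaths the study would see are about 3.0 and 3.3. With censoring at recurrence, Kaplan-Meier estimates survival under h0 alone, 0.99³ = 97% in both arms. In this example a true difference of about 8 percentage points would appear as none.

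**The case against.** The best defence is that the end-of-study sentence is loosely drafted, sits under Safety reporting and never says that vital-status contact stops. Visits and Table 1 run to 36 months with no exception at recurrence. The data collection section intends to record deaths from HCC recurrence, which is possible only if patients are followed past it. A condensed article may also leave post-recurrence contact to the full protocol.

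This shows what the authors probably intend. It does not undo the rule they wrote, and staff who followed that rule would stop. The point is therefore a stated contradiction and does not rest on something left out.

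Other parts of the defence stand and limit the point:

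- A reader might infer that OS cannot be observed at all. The documents do not support that, because deaths without prior recurrence are still captured.
- A reader might infer that the primary analysis or its ITT set loses outcomes through the recurrence rule. It does not, because the RFS event has already occurred when the rule applies.
- A reader might take it as given that patients removed for poor compliance are no longer scanned, and that removals differ by arm. The text says neither. It leaves open what they are removed from, and the ITT analysis is said to include protocol deviations. This is a matter for clarification.
- The percentages of deaths missed rest on assumed rates and move widely with them. Only the count of about 54 follows from the article's own figures.

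**Conclusion.** The point holds as an internal contradiction. The end-of-study rule cannot stand together with 3-year OS, the recording of deaths from HCC recurrence and cancer-specific survival.

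If the rule is followed, about 54 of 238 patients (about 36 ETV, 18 TDF) are censored for OS at recurrence. This rests on the planned 70% and 85% RFS. The censoring is informative and, under the trial's own hypothesis, about twice as frequent in the ETV arm. Deaths after recurrence are missed, and deaths from HCC recurrence are almost entirely unseen. The range of 25–81% for the share of 3-year deaths missed is illustrative only.

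The rule leaves deaths without prior recurrence, the primary RFS event and the sample size of 190/238 untouched. It still needs correcting, because it would give a wrong answer on the secondary endpoint and because vital-status data not collected at the time may be hard to recover.

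**What to change.** Reconcile the end-of-study definition with the Endpoints, Data collection and management, and Statistical analysis sections:

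1. State that imaging recurrence ends RFS assessment only.
2. State that vital status, date of death and cause of death are recorded for every randomised participant until 36 months after surgery, death or withdrawal of consent, by clinic visit or telephone.
3. Define OS as censored only at the date last known alive.
4. As a secondary clarification, state that removal for poor compliance does not end outcome follow-up, so that the ITT analysis has those patients' outcomes.

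The cost is a wording change, a short vital-status CRF page and contact with about 54 patients after recurrence. Vital-status contact needs no added procedures, and the sample size does not change. If removed patients would otherwise have stopped attending, item 4 also means keeping them on the imaging already scheduled until recurrence or month 36. The article does not say how many that would be.

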### Mid-term analysis

Besides final analysis, a mid-term analysis will be scheduled in the study. The purpose of mid-term analysis is about the safety and efficacy of the study. The scheduled time for mid-term analysis is set at 1 year after the last enrolled patient. If the RFS invalid hypothesis is rejected prior to final analysis, the trial might be discontinued.

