**Methods and analysis:**

This is a prospective, randomized, controlled, single-center study with two parallel groups of patients with HBV-related HCC who have received long-term ETV therapy before surgery. West China Hospital will enroll 238 patients, randomized in a 1:1 ratio to TDF switch therapy or ETV maintenance after surgery. The primary endpoint of this study is 3-year recurrence free survival (RFS), with the secondary endpoint being 3-year overall survival (OS) after curative surgery of HCC. Safety events will be diligently recorded.

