### Sample size calculation

The sample size calculation was performed using the software PASS (version 2015). The parameters were obtained from our previous randomized clinical trial, which evaluated the efficacy of TDF and ETV in early-stage HBV-related HCC patients after surgery. In that study, the 3-year RFS rates were 70.4% and 82.4% for patients receiving ETV and TDF, respectively. Assuming 3-year RFS rates of 70% for the control group and 85% for the treatment group, with a one-sided alpha of 0.05 and 80% power, the corresponding sample size is 190. Accounting for a 20% dropout rate, a total of 238 patients will be included in this study.

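### The mid-term RFS efficacy test has no boundary of its own; read as written, RFS is tested twice at 0.05 and the overall type I error is about 7.3% one-sided (7.6% two-sided)

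*Protocol article*

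**What the plan says.** The protocol article, section Mid-term analysis, plans two analyses: "Besides final analysis, a mid-term analysis will be scheduled in the study". It gives safety and efficacy as the purpose and fixes the timing: "The scheduled time for mid-term analysis is set at 1 year after the last enrolled patient". The consequence follows: "If the RFS invalid hypothesis is rejected prior to final analysis, the trial might be discontinued". I read the 'invalid' hypothesis as the null hypothesis. The section gives no significance level, boundary or spending function for this look.

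The section Statistical analysis names the log-rank test for RFS and closes with one general rule, a p-"value < 0.05 indicates statistical significance". The rule is not tied to a particular look, and no sidedness is given for the survival tests.

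The section Sample size calculation sets the design error rate: "with a one-sided alpha of 0.05 and 80% power, the corresponding sample size is 190". It makes no mention of an interim look.

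**The concern.** A null hypothesis that may be rejected at either of two looks, each at the full level, is rejected by chance more often than that level says. Here the full 0.05 is already committed to the final test. Any efficacy rejection allowed at mid-term adds to it, and the addition is negligible only if the mid-term level is very strict. The text names no strict level, and the one threshold it gives is 0.05.

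What is at stake is the false-positive rate of the primary claim. A trial stopped on a significant interim result also tends to overstate the effect. By the timing rule all patients are enrolled at this look, so a stop would save no recruitment.

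**Working it through.** **1. Reproduce the plan's own figure.** Inputs from Sample size calculation: 3-year RFS 70% and 85%, one-sided alpha 0.05, power 80%. Allocation is 1:1 (Abstract). With the pooled-variance formula for two proportions and no continuity correction, the mean proportion is 0.775 and

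n per arm = [1.645·√(2·0.775·0.225) + 0.842·√(0.70·0.30 + 0.85·0.15)]² / 0.15² = (0.971 + 0.489)² / 0.0225 ≈ 94.8, rounded up to 95.

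This gives 190 in total, and 190/0.80 = 237.5, rounded up to 238. Both figures match the protocol for a single analysis, so nothing is set aside for a second look. (A two-sided 0.05 would need 242 before dropout.)

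**2. Information at the mid-term look (assumption; the document gives no figure).** Recruitment is planned from May 2022 to May 2024, so the look falls at about May 2025 with follow-up of 12 to 36 months. Assume uniform accrual, constant hazards and 36 months of follow-up per patient.

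- Hazards per month: −ln(0.70)/36 = 0.00991 and −ln(0.85)/36 = 0.00451.
- Mean probability of an event by the look, averaging 1 − exp(−λu) over u from 12 to 36: 0.2098 and 0.1022, so 0.1560 over both arms.
- By 36 months for everyone: (0.30 + 0.15)/2 = 0.225.
- Information fraction: 0.1560/0.225 = 0.693. In 190 patients this is about 29.6 of 42.75 events.

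The fraction is about 0.82 if the hazard in the first 24 months is four times the later one. It is about 0.50 if patients are followed without a 36-month cap to August 2027, the study end in Study design.

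**3. Overall type I error with 0.05 at both looks.** Under the null, the two log-rank statistics are approximately bivariate normal with correlation √t, where t is the information fraction.

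- One-sided: 1 − P(Z₁<1.645, Z₂<1.645)
- Two-sided: 1 − P(|Z₁|<1.96, |Z₂|<1.96)

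| t | One-sided | Two-sided |
|---|---|---|
| 0.50 | 8.0% | 8.3% |
| 0.70 | 7.3% | 7.6% |
| 0.80 | 6.9% | 7.1% |
| 0.82 | 6.8% | 7.0% |

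The error stays above 5% at every fraction tried from 0.3 (8.6% and 8.9%) to 0.9 (6.3% and 6.5%).

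**4. Sidedness.** If both tests are two-sided, the error in favour of TDF alone is half the two-sided total: 7.56%/2 ≈ 3.8% at t = 0.70, and 8.3%/2 ≈ 4.2% at t = 0.50.

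**5. Check of the fix at t = 0.70.**

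- One-sided p<0.001 at mid-term (z = 3.090) and one-sided p<0.05 at the end: 1 − P(Z₁<3.090, Z₂<1.645) = 5.00%. At t = 0.50 the same formula gives 5.02%.
- Power is 80.0% against 80.0% without the look, with expected final statistic 1.645 + 0.842 = 2.486.
- Chance of crossing the boundary under the design effect: the expected mid-term statistic is 2.486·√0.70 = 2.080, so P(Z > 3.090 − 2.080) ≈ 16%.
- O'Brien-Fleming-type spending would instead need about 0.0191 and then 0.0443 one-sided. Equal (Pocock) levels would be 0.0335 one-sided at each look.

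**The case against.** The strongest objection is that the mid-term level is not written down. The threshold in Statistical analysis is a generic closing line, and boundaries are often set in an analysis plan or monitoring charter that is not shown here. A Haybittle-Peto rule in such a document would leave the final 0.05 as it stands and control the error. This holds as far as it goes: the mid-term 0.05 is a reading of the only threshold given, not an explicit statement. It does not remove the point, because this text does state an efficacy rejection with a consequence, commits the full alpha to one analysis, and points to no boundary elsewhere.

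The second objection is sidedness. The only design error rate is one-sided. If the general threshold is two-sided for RFS, the error in favour of TDF stays below that 5%. This also stands, but the two-sided test then misses its own nominal level.

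A reader might infer more than the text supports:

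- *That a mid-term rejection automatically ends the trial.* The wording makes discontinuation optional. That limits the stopping, not the inflation, if a positive result can be declared at either look.
- *That RFS cannot be tested at mid-term because few patients have reached 36 months.* The section Endpoints defines RFS as a time in months, and a log-rank test is valid on censored times.
- *That third-year RFS and OS data would be lost.* The protocol does not say follow-up ends on discontinuation. It leaves this open, which is a reason to state it.

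**Conclusion.** The point holds as a conditional but well-supported one. Taken at its word, the protocol tests RFS twice at 0.05, and the overall type I error is about 7.3% one-sided or 7.6% two-sided, roughly 2 to 3 percentage points above nominal. Over information fractions from 0.82 to 0.50 the range is 6.8% to 8.3%. The size rests on the information fraction, which is assumed, and on the general threshold applying at the mid-term look. For any unadjusted second test at 0.05 the direction does not depend on the fraction. Under two-sided tests the false-positive rate in favour of TDF alone is about 3.8%, so it would be wrong to say that the one-sided 5% is exceeded on every reading. The boundary should be settled before any comparative RFS data are examined.

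**What to change.** State a mid-term efficacy boundary in Mid-term analysis, for example Haybittle-Peto at one-sided p<0.001, and keep the final RFS test at the design's own level and sidedness, one-sided 0.05. Say in Statistical analysis that the general threshold does not apply to the mid-term look, and give the sidedness of the RFS test. The alternative is a mid-term look without an efficacy rejection, which leaves 0.05 valid at the end but gives up the efficacy purpose the protocol now states.

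Add that RFS and vital-status follow-up continue to 36 months for all patients if the boundary is crossed.

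The cost is a few sentences and no extra patients. An early efficacy stop becomes unlikely: about 16% under the design effect at t = 0.70. The final test should not be changed to two-sided 0.05 in passing, because at 95 per arm that lowers power from 80.1% to 70.0%.

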### Randomization and allocation

Block randomization with a block length of four will be employed. For each block, enrolled participants will undergo 1:1 randomization into the continuing-ETV therapy group and the switch-TDF therapy group. Randomization numbers will be generated using STATA/SE 15.1 and sealed in envelopes.

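### RFS may be rejected at the mid-term look and again at the final analysis under a single p < 0.05 rule, so a one-sided 5% trial becomes roughly a 7.3% trial

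*Protocol article*

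**What the plan says.** Three parts of the protocol article bear on this.

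- **Mid-term analysis.** The section opens with "Besides final analysis, a mid-term analysis will be scheduled in the study", gives safety and efficacy as its purpose, and times it one year after the last patient is enrolled. It then says: "If the RFS invalid hypothesis is rejected prior to final analysis, the trial might be discontinued". In context, the invalid hypothesis can only sensibly be the null hypothesis. No significance level is printed in this section.
- **Statistical analysis.** RFS is compared by the log-rank test. The section closes with the article's only decision rule: "A *p*-value < 0.05 indicates statistical significance". It makes no exception for the mid-term look and gives no side for the RFS test.
- **Sample size calculation.** The assumptions are "Assuming 3-year RFS rates of 70% for the control group and 85% for the treatment group", and the result is stated "with a one-sided alpha of 0.05 and 80% power, the corresponding sample size is 190". The mid-term look is not mentioned.

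**The concern.** The mid-term section makes the look a formal test of the primary endpoint that can end the trial. The only threshold available for that test is the same p < 0.05 that applies at the end, and nothing is held back for the second test. The RFS null hypothesis can therefore be rejected on two occasions, each at the full level, although the error rate in the sample size section holds only for one test.

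At stake is the error rate of the primary conclusion. If switching has no effect, a difference would be declared about one and a half times as often as the nominal level implies. Making the stop optional does not help, because the error is the same whenever a rejection at either look counts as success.

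**Working it through.** **1. Reproduce the plan's sample size.** Inputs: 70% and 85% RFS at 3 years, one-sided 0.05, 80% power (Sample size calculation), and 1:1 allocation (Randomization and allocation). With pooled variance and no continuity correction, and mean rate 0.775:

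n per arm = [1.645·√(2·0.775·0.225) + 0.842·√(0.70·0.30 + 0.85·0.15)]² / 0.15² = 94.8, rounded up to 95.

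This gives 2 × 95 = 190, and 190 / 0.80 = 237.5, rounded up to 238. Both published figures match. A two-sided test would give 242 and a one-sided test with continuity correction 216, before dropout. The plan is therefore a fixed, single-look design using all of one-sided 0.05.

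**2. Information at the look.** The article states no information fraction, so it is derived from the dates: accrual May 2022 to May 2024 (24 months), look 12 months after the last enrolment, 36 months of follow-up per patient. Assuming uniform accrual, follow-up at the look is uniform on 12 to 36 months. With a constant hazard, the fraction t is the mean of 1 − S(u) over that range, divided by 1 − S(36):

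| 3-year RFS | Events at look | Events at 36 months | t |
|---|---|---|---|
| 70% | 0.2098 | 0.300 | 0.699 |
| 77.5% (pooled) | 0.1553 | 0.225 | 0.690 |
| 85% | 0.1022 | 0.150 | 0.682 |

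Other assumptions move t. Front-loaded recurrence (Weibull shape 0.8 to 0.5) gives about 0.74 to 0.83. Counting events up to August 2027 gives about 0.50 to 0.53. A range of 0.50 to 0.85 covers these.

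**3. Overall type I error with nominal 0.05 at both looks.** Under the null hypothesis the two log-rank statistics are approximately bivariate normal with correlation √t, and the overall error is 1 − P(no rejection at either look).

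| t | One-sided 0.05 twice (1.645) | Two-sided 0.05 twice (1.96) |
|---|---|---|
| 0.50 | 8.0% | 8.3% |
| 0.60 | 7.7% | 8.0% |
| 0.70 | 7.3% | 7.6% |
| 0.80 | 6.9% | 7.1% |
| 0.85 | 6.6% | 6.8% |

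**4. False claims for TDF only, if the tests are two-sided.** Only the upper limit of 1.96 counts. At t = 0.70 this gives 3.8%, against 2.5% for one look. The ratio is 3.8/2.5 ≈ 1.5, and 7.3/5 ≈ 1.5 on the one-sided scale.

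**5. Levels that restore 5% at t = 0.70.** Lan-DeMets O'Brien-Fleming-type spending gives 0.0191 then 0.0443 for overall one-sided 0.05, and 0.0148 then 0.0455 for overall two-sided 0.05. A Pocock-type boundary gives about 0.034 (one-sided) or 0.032 (two-sided) at each look.

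**6. Power cost at the final look.** The hazard ratio is ln(0.85)/ln(0.70) = 0.456. The 190 evaluable patients give 190 × 0.225 ≈ 43 events. Schoenfeld drift: |ln 0.456|·√43 / 2 = 2.58.

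- One-sided: 82.4% at 0.05, 80.9% at 0.0443 (1.5 points).
- Two-sided: 73.1% at 0.05, 71.8% at 0.0455 (1.3 points).
- If all 238 patients contributed (about 53 events), two-sided: 81.6% to 80.5% (1.1 points).

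**The case against.** The best counter-argument is that the mid-term section prints no level. The 0.05 at the look is inferred from a general closing sentence that follows baseline comparisons as well as survival methods. This is a condensed article, and boundary values are commonly left to an analysis plan, which could set one. It stands that the level is inferred and that the absence of boundary values would be no finding in itself. But the article does more than stay silent: it sets an efficacy stopping rule, one unqualified threshold, and a sample size that spends all of alpha on one analysis. Followed together, these give the wrong error rate.

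The second argument concerns sidedness, and it stands. The only stated rate is one-sided 5%. A reader might set the two-sided 7.6% against it and conclude that the stated rate is wrong under any reading. The documents do not support that: two-sided p < 0.05 at both looks gives 3.8% for a false TDF claim, which is below 5% though above the 2.5% for one look.

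A reader might also infer that 0.05 at the look is far looser than any group-sequential design allows. That holds against O'Brien-Fleming-type levels. A Pocock-type design allows about 0.032 to 0.034.

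Finally, the Discussion's account of early recurrence favours front-loaded events, which raise t and bring the error slightly below 7%. No fraction in the range considered brings it back to 5%.

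**Conclusion.** The point holds in conditional form. If p < 0.05 is applied at both looks, as the text allows, a one-sided test has an overall type I error of about 7.3% at 70% information instead of the stated 5%. The two-sided equivalent is about 7.6%.

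This rests on reading the general p < 0.05 rule as covering the mid-term look, on counting a rejection at either look as success, and on an information fraction derived from the stated dates under assumed uniform accrual and constant hazard. The size depends only weakly on that fraction. It does depend on the sidedness of the RFS test, which the statistical section does not state.

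**What to change.** Change two sections before any RFS comparison by arm is seen.

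- **Statistical analysis:** state whether the RFS test is one- or two-sided, and replace the flat 0.05 for RFS by the level remaining at the final analysis.
- **Mid-term analysis:** test RFS only against a pre-specified boundary, for example Lan-DeMets O'Brien-Fleming-type, computed from the events actually observed. The levels in step 5 (0.0191 then 0.0443 one-sided, 0.0148 then 0.0455 two-sided) are illustrations at 70% information. The one-sided pair matches the sample size section.

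Alternatively, declare the look safety-only with no RFS test and keep 0.05 for the final analysis. This costs no power.

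With the boundary, no patients are added, and about 1 to 1.5 percentage points of final-look power are lost, partly recovered by the chance to reject at the look. Choosing two-sided 0.05 is a larger change than the split itself: with about 43 events, power is already below 80% before any alpha is spent at the look.
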